#### Cohort of pregnant women

The data will be collected following a cohort of pregnant women presenting to antenatal care visits. We shall have both a retrospective cohort for the period January 2018 to December 2021 to determine the Impact of COVID-19 pandemic on malaria control and a prospective cohort for the period July 2022 to June 2024 to determine the incidence of malaria related adverse maternal and foetal outcomes. For the prospective cohort, recruitment will take place at ANC clinic. Collected data will explore the practices towards malaria prevention during the COVID-19 pandemic, malaria and COVID risk-perception and use of insecticide-treated nets, while and follow up will investigate access to antenatal care visits, administration of IPTp, healthcare seeking behaviour in case of fever. Follow-up will end at delivery, when maternal and foetal outcomes will be collected.

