### Sample size estimation

#### Sample size estimation

COVID-19 impact population

For the retrospective cohort investigating the impact of COVID-19, we shall use a *facility-based census* to include all pregnant mothers who sought care at the study sites for the period January 2018 to December 2021.Prospective çohort of pregnant women

For the prospective cohort, the sample size was estimated using the sample size estimation function in STATA12 for two-sample comparison of proportions. Null hypothesis: p1 = p2, (no difference in preterm birth rates), where p1 is the preterm birth rate among pregnant mothers diagnosed with malaria (exposed group) and p2 is the preterm birth rate among pregnant mothers with no diagnosis of malaria (non-exposed group). Assuming a type I error, alpha, of 0.050 for two-sided hypothesis, power of the study at 0.80, p1 = 0.075 and p2 = 0.039 based on the preterm birth rates reported in the Uganda Birth Cohort Study conducted from 2014–2016 in 12 districts in rural northern and southwestern Uganda [20]. Assuming equal number of participants in both groups, the required sample sizes in each of the two groups is 705. And after factoring in 10% for non-response in both groups, the total minimum required sample size is 1552 pregnant women (776 in each of the 2 groups).Antimalarial resistance population

Given the total population of 779,600 in Oyam and Kole districts. Given that, based on Uganda bureau of statistics (UBOS), the total number of pregnant women in the two districts is expected to be 5% of the total population (n = 38,980); the expected rate of parasitemia among pregnant mother is expected to be 27% (n = 10,525) [21]; the expected resistance to sulfadoxine-pirimethamine and artemisinin-derivatives are, respectively, 16% and 20% [16, 18]; using the sample size calculation formula developed by Daniel and colleagues [22] and a margin of error, alpha = 5% the minimum required number of pregnant women diagnosed with malaria is 203. Applying 10% correction factor and assuming an increasing trend the required minimum sample size for this population is 224 cases of microscopically confirmed malaria among pregnant women.

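### The cohort's 10% allowance is added (705 x 1.1) rather than divided out (705 / 0.9), so a 10% loss leaves about 698 per group; it is also labelled non-response although the outcome is lost between enrolment and delivery (minor)

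*Protocol article*

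**What the plan says.** The section Sample size estimation compares preterm birth between women with and without a malaria diagnosis. The inputs are given as "Assuming a type I error, alpha, of 0.050 for two-sided hypothesis, power of the study at 0.80", with "p1 = 0.075 and p2 = 0.039 based on the preterm birth rates reported in the Uganda Birth Cohort Study". The result is: "Assuming equal number of participants in both groups, the required sample sizes in each of the two groups is 705". The allowance follows: "after factoring in 10% for non-response in both groups, the total minimum required sample size is 1552 pregnant women", which the article breaks down as "776 in each of the 2 groups".

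Two other places bear on what the allowance has to cover. Sampling procedure and selection of participants has eligible women enrolled consecutively until the minimum size is reached. Study design, under the cohort of pregnant women, fixes when the outcome becomes known: "Follow-up will end at delivery, when maternal and foetal outcomes will be collected".

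**The concern.** An allowance for lost data should leave the required number after the loss has happened. Adding 10% to the requirement does not do that, because the 10% is later lost from the larger, inflated number. The article calls 1,552 a minimum and ties the end of enrolment to the minimum, so no surplus is planned to absorb the difference.

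The second issue is what the 10% is for. Non-response normally means women who are approached and do not take part. Under consecutive enrolment up to a fixed number, such women are replaced by the next eligible woman and do not reduce the enrolled total. An enrolled woman whose delivery outcome is never recorded does reduce it. Women may enter at any gestational age, so the interval in which this can happen may be long. If the 10% is spent on the wrong kind of loss, the stated size gives no view of how power depends on retention to delivery.

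**Working it through.** **Inputs** (all from Sample size estimation): p1 = 0.075, p2 = 0.039, difference d = 0.036, two-sided alpha 0.05 (z = 1.960), power 0.80 (z = 0.8416), equal groups, 705 per group before and 776 after the allowance.

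**1. Reproduce 705.**
Mean proportion = (0.075 + 0.039)/2 = 0.057.
n = [1.960 x sqrt(2 x 0.057 x 0.943) + 0.8416 x sqrt(0.075 x 0.925 + 0.039 x 0.961)]² / 0.036² = 649.9.
With the continuity correction: n/4 x [1 + sqrt(1 + 4/(n x d))]² = 704.3, rounded up to 705.
The stated figure reproduces, and it is the continuity-corrected one. Without the correction the requirement is 650.

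**2. Reproduce 776 and 1,552.**
705 x 1.1 = 775.5, rounded up to 776; 776 x 2 = 1,552. The allowance was added to the requirement.

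**3. Apply a 10% loss.**
776 x 0.9 = 698.4 per group, against 705 required (1,396.8 against 1,410 in total).
To keep 705 after a 10% loss: 705 / 0.9 = 783.3, rounded up to 784 per group, or 1,568 in total, which is 16 more than stated.
Largest loss that still leaves 705 per group: 1 - 705/776 = 9.1%.

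**4. What that does to power.**
Continuity-corrected power = Φ{[d - 1/n - 1.960 x se0] / se1}, where se0 = sqrt(2 x 0.057 x 0.943 / n) and se1 = sqrt[(0.075 x 0.925 + 0.039 x 0.961)/n]. The uncorrected version omits the 1/n term.

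| Loss before delivery | Women left per group | Power, continuity-corrected | Power, uncorrected |
|---|---|---|---|
| 10% | 698.4 | 79.6% | 82.8% |
| 20% (assumed) | 620.8 | 74% | 78% |
| 30% (assumed) | 543.2 | 68% | 73% |

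The article gives no expected loss to delivery, so the 20% and 30% rows are assumptions. All rows keep the plan's equal groups and take the loss to be the same in both.

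**The case against.** The strongest defence is that nothing here changes the study. Factoring in 10% does not by itself prescribe division by 0.9. Adding 10% is a common, slightly less protective convention, and the sum is internally consistent. The section Data analysis names chi-squared tests without mentioning a continuity correction. On the uncorrected basis 650 per group suffice, 698 per group still exceeds 80% power, and 776 tolerates 1 - 650/776, or about 16%, loss. Non-response is undefined in a condensed article and may loosely include women without outcome data. Planning to deliver in the hospital is an inclusion criterion, which should limit the loss.

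Most of this stands as a limit on size. It does not remove the point: 705 is the article's own requirement, and the stated minimum does not preserve it after a 10% loss. The entry criterion records an intention; it is not an allowance for women who deliver elsewhere or stop attending.

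A reader might extend the criticism to the antimalarial resistance population, where 203 x 1.1 = 223.3 becomes 224. The article does not support that. Its words are "Applying 10% correction factor and assuming an increasing trend the required minimum sample size for this population is 224 cases". The 10% there is a correction factor linked to an expected trend, in a cross-sectional sample with no follow-up to delivery. No loss is stated, so there is no loss against which 224 falls short.

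**Conclusion.** The point holds for the prospective cohort and is minor. The 10% is applied as a multiplier of 1.1, so a 10% loss leaves about 698 per group where 705 are required. The gap is 16 women in 1,552, about 1%, and costs about 0.4 percentage points of power on the basis used to obtain 705.

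The label is the more useful part. As written, the allowance is for non-response, which consecutive enrolment already makes good, while loss between enrolment and delivery has no named allowance. This rests on reading non-response in its usual sense; if loss to follow-up was meant as well, the text is ambiguous and should say so.

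A reader might infer that the cohort is underpowered, or that 9.1% is a hard ceiling on tolerable loss. Neither follows. The 9.1% is the loss at which 705 per group is just preserved, and 705 contains the continuity correction; for an uncorrected chi-squared test the corresponding figure is about 16%. The lower powers in the table depend on loss rates that the article does not give.

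**What to change.** In Sample size estimation, for the cohort only, do one of two things:

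- restate the minimum as 705 / 0.9 = 784 per group, 1,568 in total; or
- keep 776 and 1,552 and state that they preserve 705 per group up to a 9.1% loss.

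In either case, replace the term non-response with a definition of the allowance as enrolled women without a delivery outcome. Optionally, add the power at assumed losses of 10%, 20% and 30% (about 80%, 74% and 68% with the continuity correction; 83%, 78% and 73% without), and say which basis matches the planned test.

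The cost is a sentence or two. The first option adds 16 women; the second adds none. The figure of 224 for the resistance population needs no change on this ground.

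### The resistance sample of 203 (224 with the 10% factor) fits only the 16% SP rate; the protocol's own 20% artemisinin rate needs 241 (266)

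*Protocol article*

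**What the plan says.** Under Sample size estimation, the paragraph on the antimalarial resistance population builds its number in steps. Pregnant women in the two districts are "expected to be 5% of the total population (n = 38,980"), and "the expected rate of parasitemia among pregnant mother is expected to be 27% (n = 10,525"). Two planning prevalences follow: "the expected resistance to sulfadoxine-pirimethamine and artemisinin-derivatives are, respectively, 16% and 20"%. The method is named but not written out ("using the sample size calculation formula developed by Daniel and colleagues"). The precision and a single number then appear together: "margin of error, alpha = 5% the minimum required number of pregnant women diagnosed with malaria is 203". After a 10% correction factor and an assumption that resistance is rising, "the required minimum sample size for this population is 224 cases of microscopically confirmed malaria among pregnant women".

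Markers for both drugs are targets. Under Study design, the section on this population names artemisinin derivatives and SP, and the section on assessing drug resistance lists *Pfk13* alongside *Pfdhfr* and *Pfdhps*. Under Sampling procedure and selection of participants, consecutive enrolment continues until the minimum sample size is met.

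**The concern.** The plan has two prevalences to estimate, one margin and one minimum. Below 50%, p(1 − p) rises with p, so the larger of the two rates needs more women for the same margin. A minimum meant to serve both drugs must be the larger of the two requirements. If it was computed at 16%, it falls short for the drug expected at 20%.

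Estimating artemisinin-marker prevalence is one of the main purposes of this population. Because enrolment is tied to the minimum, too small a figure could end recruitment before the stated precision is reached. The wording also treats the margin of error and alpha as the same quantity, although the preceding paragraph of the same section uses alpha for the type I error. The reader is therefore not told the confidence level.

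**Working it through.** **Inputs**, all from Sample size estimation unless marked:
- N = 10,525 parasitaemic pregnant women (27% of 38,980)
- p = 0.16 (SP) and p = 0.20 (artemisinin derivatives)
- margin d = 0.05
- z = 1.96, that is 95% confidence (assumed, not stated separately)
- 10% correction factor

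**Formula.** The article does not print its formula. I used the usual one for a single proportion with a finite population:

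n = N z² p(1 − p) / [d² (N − 1) + z² p(1 − p)]

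**Step 1: reproduce the plan's figure at p = 0.16.**
- z² p(1 − p) = 3.8416 × 0.1344 = 0.5163
- d² (N − 1) = 0.0025 × 10,524 = 26.31
- n = 10,525 × 0.5163 / (26.31 + 0.5163) = 202.6, rounded up to **203**
- 203 × 1.10 = 223.3, rounded up to **224**

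Both printed figures are matched exactly.

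**Step 2: the same calculation at p = 0.20.**
- z² p(1 − p) = 3.8416 × 0.16 = 0.6147
- n = 10,525 × 0.6147 / (26.31 + 0.6147) = 240.3, rounded up to **241**
- 241 × 1.10 = 265.1, rounded up to **266**

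The shortfall is 241 − 203 = 38 women before the factor and 266 − 224 = 42 after it. Since 241/203 = 1.19, about 19% more women are needed.

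**Step 3: could 203 come from 20% in some other way?**

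| Variant | n before the 10% factor |
|---|---|
| p = 0.20, no finite-population term | 246 (271 with the factor) |
| p = 0.20, N = 38,980 | 245 |
| p = 0.20, 90% confidence, no finite-population term | about 173 |
| p = 0.18 (mean of the two rates), N = 10,525 | 223 |
| p = 0.16, no finite-population term | 207 |
| p = 0.16, N = 38,980 | 206 |

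None gives 203. Only p = 0.16 with N = 10,525 does.

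**Step 4: precision delivered.** Half-width = 1.96 √[p(1 − p)/n], multiplied by √[(N − n)/(N − 1)] for the finite population.

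| p | n | With finite-population term | Without |
|---|---|---|---|
| 0.16 | 203 | 4.99 points | 5.04 points |
| 0.20 | 203 | 5.45 points | 5.50 points |
| 0.20 | 224 | 5.18 points | 5.24 points |

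The 5-point margin is met for SP at 203. It is missed for artemisinin at 203, and at 224 even if every sample can be analysed.

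**The case against.** The arithmetic is hard to dispute, and no documented reading makes 20% yield 203. The case on the other side concerns weight and wording.

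- **The loss is small.** This is a descriptive, cross-sectional prevalence estimate. No test or decision threshold depends on the 5-point margin, and the article says that the molecular results do not affect patient management. A half-width 0.2 to 0.5 points wider leaves a usable, unbiased estimate. This stands and limits how much the point matters.
- **The basis is inferred.** The article does not say that only the 16% rate was used, nor that confidence is 95%. This also stands, but the exact match of both 203 and 224 makes the inference strong.
- **The 10% may not be purely for attrition.** The text ties it to rising resistance. If all of it may count towards precision, the comparison is 224 against 241, a gap of 17. The gap narrows but does not close, and a prevalence rising towards 50% would need more women, not fewer.
- **The planning rates are uncertain and the sites are not random.** The Background gives the sextuple haplotype as 3.9% at baseline and 16.7% after one SP dose, and three facilities are chosen purposively. So 241 would not by itself guarantee 5 points. That is true, but it does not justify a minimum that fails on the plan's own inputs.
- **The cohort may supply enough positives anyway.** Applying 27% to the 1,552 cohort women gives about 419, where the half-width at 20% would be about 1.96 × √(0.16/419) = 3.8 points. This is only indicative. It assumes that the district rate holds in the cohort, and it ignores the exclusion for prior antimalarial intake, the separate consent for shipping samples and the restriction to *P. falciparum*.

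**Conclusion.** The concern holds. On the protocol's own inputs, 203 and 224 are the requirement for the 16% SP rate. The 20% artemisinin rate requires 241, or 266 with the same factor, and the stated 5-point margin becomes 5.4 to 5.5 points at 203 and 5.2 at 224.

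This rests on two inferences: 95% confidence, and the single-proportion formula with N = 10,525. Reproducing both printed figures exactly supports them. Without the finite-population term the requirement at 20% is slightly larger (246, or 271 with the factor), so the conclusion does not depend on that term. Nor does it depend on which drug carries which rate, because the larger rate governs either way. The loss of precision is modest, but the stated minimum does not deliver what the plan claims for it.

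**What to change.** Make one of two corrections under Sample size estimation:

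1. Restate the minimum as 241 evaluable women, or 266 with the 10% factor, and say that the 20% rate governs; or
2. Keep 203 and 224, and state the margin as 5 points for SP and about 5.5 points for artemisinin derivatives at 203 evaluable women (5.2 at 224).

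In either case, replace the merged label with a margin of error d = 5% at 95% confidence, if that is what was intended, and say which prevalence the number was computed for.

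The second option changes only the text. The first raises the target by 42 confirmed cases. Table 1 already sends positive cohort samples for genotyping, so those cases may arise without extra recruitment if something near the indicative 419 positives is reached. That should be checked against actual accrual and the eligibility and consent rules, not assumed.

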#### Antimalarial resistance population

To estimate the epidemiological burden of resistance to first-line drugs for treatment and prevention of malaria in pregnant women, a separate sub-population of women diagnosed with positive malaria parasitaemia will be recruited. Prevalence of antimalaria resistance will be evaluated with a cross-sectional analysis of genetic polymorphisms in plasmodium parasites isolated from blood samples collected for the period July 2022 to June 2024. Individuals eligible for this subpopulation will be all pregnant women presenting with microscopically confirmed *P. falciparum* malaria in the study sites. For individuals included in this population, clinical data will be collected, and blood samples to be sent to Italian National Institute of Health, Rome, for detection of genetic markers of resistance to artemisinin derivatives and sulfadoxine-pyrimethamine.

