### Sampling procedure and selection of participants

Sampling of health Units: The study will use purposive sampling to include Aber Hospital, Aboke HCIV and Atipe HCIII as the site for enrollment. This is based on the following criteria:Already existent good laboratory capacity for diagnosis of malaria.Presence of an experienced microscopist.Antenatal care visit volumes of at least 50 visits per month.Good quality of routine service offered to patients with malaria as per periodic quality of care assessment.

Participants coming to the sampled in healthcare facilities that will meet the eligibility criteria will be included in the study. Consecutive enrollment of participants will be undertaken up to when the minimum sample size required for the study will be met.

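### The resistance sample is defined as P. falciparum in one section but targeted and stopped on microscopy-confirmed malaria of unstated species, and not on typed P. falciparum infections

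*Protocol article*

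**What the plan says.** The Protocol article describes the resistance population in several places.

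- **Study design, Antimalarial resistance population:** eligible women are those "presenting with microscopically confirmed *P. falciparum* malaria in the study sites".
- **Eligibility criteria, Antimalarial resistance population:** malaria must be confirmed by microscopy. No species is named.
- **Sample size estimation:** the precision calculation gives 203 women with malaria. This is then raised by a tenth, with a rising trend mentioned in the same sentence, and the result is stated as follows: "the required minimum sample size for this population is 224 cases of microscopically confirmed malaria among pregnant women". Again no species is named.
- **Sampling procedure and selection of participants:** "Consecutive enrollment of participants will be undertaken up to when the minimum sample size required for the study will be met".
- **Microscopy:** the thin smear identifies the species.
- **Advanced analysis of polymorphism, and Table 1:** PCR follows microscopy, to confirm it and to separate the species. It can return P. vivax, P. malariae or P. ovale.
- **Assessment of Plasmodium falciparum drug resistance:** resistance is read by sequencing Pfk13, Pfdhfr and Pfdhps, all of them P. falciparum genes.
- **Ethical considerations:** collecting and shipping blood samples needs a second consent.

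**The concern.** Two things do not fit together. First, the article gives two definitions of the same population: P. falciparum in Study design, and malaria of unstated species in the inclusion list and the target. Second, even with the species aligned, the target is counted at the smear, while the estimate exists only for infections that pass PCR and sequencing. A counted case can fail to give a result because PCR finds another species, because PCR is negative, or because sequencing fails.

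If enrolment stops on the smear count, the target can be declared met before the reference laboratory has shown how many infections are usable. What is at stake is the precision of the prevalence estimates, which is the only criterion on which this sample was sized.

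**Working it through.** **Inputs** (all from Sample size estimation unless noted)

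- Infected pregnant women: 779,600 × 5% = 38,980; × 27% = 10,525 = N.
- Expected prevalence of resistance: 16% (SP) and 20% (artemisinin derivatives).
- Precision: "a margin of error, alpha = 5" per cent, read here as a margin d = 0.05. The text merges margin and alpha, so 95% confidence (z = 1.96) is an assumption.
- Share of counted cases that cannot be typed: not given, so it is varied below.

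**Step 1. Reproduce the plan's figure.**

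n = N z² p(1−p) / [d²(N−1) + z² p(1−p)]

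- p = 0.16: z² p(1−p) = 3.8416 × 0.1344 = 0.5163. So n = 10,525 × 0.5163 / (26.31 + 0.5163) = 202.6, rounded up to 203.
- 203 × 1.10 = 223.3, rounded up to 224.

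Both stated figures reproduce. Other prevalences do not give 203: p = 0.18 gives 223 and p = 0.20 gives 241. The 203 is therefore the SP calculation.

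**Step 2. Size of the reserve.**

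224 − 203 = 21 cases, and 21/224 = 9.4%. Typed infections fall below 203 only if more than 9.4% of counted cases are lost. The factor was applied as 203 × 1.1. To absorb a full 10% loss, 203/0.90 = 225.6, or 226, would be needed.

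**Step 3. Margin actually reached, by assumed loss.**

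Half-width = 1.96 × √[p(1−p)/m × (N−m)/(N−1)], with m = 224 × (1 − loss).

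| Assumed loss | Typed m | SP, p = 16% (points) | Artemisinin, p = 20% (points) |
|---|---|---|---|
| 0% | 224.0 | 4.75 | 5.18 |
| 5% | 212.8 | 4.88 | 5.32 |
| 9.4% | 203.0 | 4.99 | 5.45 |
| 10% | 201.6 | 5.01 | 5.47 |
| 15% | 190.4 | 5.16 | 5.63 |
| 20% | 179.2 | 5.32 | 5.81 |
| 30% | 156.8 | 5.70 | 6.21 |

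If losses are independent between samples (binomial, 224 cases), the chance of fewer than 203 typed is 0.2% at 5% loss, 19% at 8%, 57% at 10% and 99% at 15%.

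**Step 4. The second marker.**

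At p = 0.20: z² p(1−p) = 0.6147, so n = 10,525 × 0.6147 / (26.31 + 0.6147) = 240.3, or 241. With all 224 typed the margin is already 5.18 points. For artemisinin there is no reserve at all.

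**Step 5. Enrolment needed, by assumed loss.**

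| Assumed loss | For 203 typed (SP) | For 241 typed (artemisinin) |
|---|---|---|
| 5% | 214 | 254 |
| 10% | 226 | 268 |
| 15% | 239 | 284 |
| 20% | 254 | 302 |

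**The case against.** The case for leaving the plan alone has several parts.

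- **Species.** Study design does restrict the population to P. falciparum, the thin smear can show the species at enrolment, and at spontaneous visits Table 1 sends samples for typing only when microscopy shows P. falciparum. A reader might infer that the plan admits every species as a rule. The documents do not support that; they contradict themselves. The contradiction stands because the inclusion list and the target are what sites work from.
- **Reserve.** The 10% factor already covers losses up to 9.4%, and no loss rate is given. A reader might infer that the sample will fall short. The text shows only that nothing rules this out. The factor's purpose is not stated, whereas the prospective cohort's 10% is labelled as non-response.
- **Supply.** Table 1 sends every positive sample from recruitment and antenatal visits for typing, and the cohort plans 776 women with malaria; even a 70% yield would give about 543 (776 × 0.7). The 224 is called a minimum, collection runs from July 2022 to June 2024, and the stopping sentence is general. This makes a shortfall less likely. However, Study design calls the resistance population separate, so the overlap cannot be relied on.
- **Bias.** A reader might infer that untyped samples would be counted as not resistant, pulling prevalence down. Nothing says so. Table 1 sends only P. falciparum-positive samples to resistance analysis, and denominator rules are commonly left to an analysis plan that is not shown here.
- **Consent.** Nothing says that a woman who declines sample shipment still counts toward 224, so no loss is attributed to this.

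**Conclusion.** The contradiction over species and the wrong counting unit are real, and both lie in matters that the article itself fixes: eligibility, target and the end of enrolment. The effect on precision is modest. For SP the stated 5-point margin holds up to a 9.4% loss; it would be about 5.2 points at 15% loss and 5.3 at 20%. These loss rates are assumptions, as is 95% confidence. No bias in the prevalence estimate is established.

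One part does not depend on any assumed loss. The 203 is not the number needed for both markers. The plan's own 20% figure for artemisinin needs 241, and its margin is about 5.2 points with all 224 typed and 5.4–5.5 with 203 typed. A correction that set 203 as the typed target for every marker would carry this error forward.

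**What to change.** 1. Reconcile Study design, Eligibility criteria and Sample size estimation by naming P. falciparum, as identified on the thin smear, in both the inclusion criterion and the target.
2. Express the target as typed P. falciparum infections: confirmed by PCR, with a readable sequence for the marker. Keep 224 as the enrolment number, and say that its 10% is the allowance for samples that cannot be typed. Applied as × 1.1, it covers 9.4%; a full 10% would need 226.
3. Do not use 203 for both markers. Either size on the 20% artemisinin figure (241 typed, or 268 enrolled at an assumed 10% loss), or keep 224 and restate the artemisinin margin as about 5.2 points with 224 typed and 5.4–5.5 with 203.
4. Report each marker's prevalence with the number typed and the margin actually reached.

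The cost is wording in three sections, plus somewhat longer sampling if the larger number is chosen or untyped cases are replaced. Table 1 already sends positive samples from antenatal visits for typing. If sampling cannot be extended, restating the margins is enough.
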